## Abstract

**Background:**

Less invasive surfactant administration (LISA) is a way of giving surfactant without endotracheal intubation and has shown to be promising in reducing the incidence of bronchopulmonary dysplasia (BPD) in preterm infants. However, the mechanism underlying its beneficial effect and variations in the technique of administration may prevent its widespread use. This trial aims to evaluate the effects of two methods of surfactant administration, LISA or endotracheal surfactant administration followed by low peak pressure (LPPSA) ventilation, in preterm infants with respiratory distress syndrome (RDS).

**Methods:**

The **L**ISA **O**r **L**ow **P**eak **P**ressure trial is to be conducted in 14 tertiary neonatal intensive care units in China. A total of 600 preterm infants born with gestational age between 25^0/7^ and 31^6/7^ weeks and with a primary diagnosis of RDS will be involved in the study. Infants will be randomized to the LISA or LPPSA group when surfactant therapy is indicated. Primary outcomes include mortality, severity of bronchopulmonary dysplasia at 36 weeks of postmenstrual age (PMA), and mechanical ventilation (MV) in the first 72 h of life. Secondary outcomes include the days of MV, duration of all sorts of non-invasive respiratory support, fraction of inspired oxygen, oxygen saturation before and after surfactant administration, and time required to perform the procedure for surfactant administration. The incidence of comorbidities, including retinopathy of prematurity (ROP), necrotizing enterocolitis (NEC), intraventricular hemorrhage (IVH), hemodynamically significant patent ductus arteriosus (hsPDA), pneumothorax, and massive pulmonary hemorrhage within 48 h of surfactant administration, and the failure rates of each technique will be determined.

**Discussion:**

Data from recent systematic review and meta-analysis have suggested a possible improvement in outcomes of preterm infants with RDS by the LISA technique. However, robust evidence is lacking. Why LISA plays a potential role in reducing respiratory morbidity, mainly BPD in preterm infants, remains unclear. The possible explanations are the active and uninterrupted delivery of continuous positive airway pressure during the LISA procedure and the avoidance of complications caused by intubation and relatively high pressure/volume ventilation following surfactant administration. We hypothesized that LISA’s effectiveness lies mainly in avoiding relatively high-pressure positive ventilation immediately following surfactant administration. Thus, this multicenter randomized controlled trial will focus on issues of endotracheal intubation and the pressure/volume used during conventional surfactant administration. The effectiveness, safety and comorbidities of preterm infants following LISA or LPPSA will be evaluated.

**Trial registration:**

Chinese Clinical Trial Registry: ChiCTR1900020970. Registered on 23 January 2019.

## Background

In the last several years, dramatic improvements have been made in the management of respiratory distress syndrome (RDS) in preterm infants, including early establishment of FRC by noninvasive respiratory support, early rescue instead of prophylactic surfactant use, and curtailed application of mechanical ventilation (MV). All these changes have greatly improved the outcome for babies with RDS [1, 2].

Less invasive surfactant administration (LISA), as an innovative mode of surfactant delivery, is getting increasing attention in the management of preterm infants with RDS. This technique is characterized by the use of a thin catheter to deliver surfactant instead of an endotracheal tube and by keeping continuous positive airway pressure (CPAP) support during the course of administration [3]. A recent systemic review and meta-analysis in preterm infants with RDS indicated that surfactant administration via the LISA method decreased the combination rate of mortality or bronchopulmonary dysplasia (BPD) and reduced need for MV during the first 72 h of life [4]. However, the implementation of the technique requires an experienced clinician and consistence when performing the procedure. Moreover, the mechanisms underlying the beneficial effect of LISA over conventional methods are not fully understood, and further research is warranted [5]. While the intubation-surfactant-extubation (INSURE) technique as a conventional method has been widely used, evidence on superiority, efficacy, and safety of the LISA method over conventional surfactant administration are needed.

To provide more evidences and elucidate the potential protective mechanisms of the LISA method, we therefore conduct a multicenter, prospective, randomized controlled trial in China. This trial aims to compare the effects of the LISA method with those of endotracheal surfactant administration immediately followed by positive pressure ventilation with a designated lower peak pressure than it does in INSURE (LPPSA) in preterm infants with RDS and indicated for surfactant administration. Our hypothesis is that the effects of designated low positive pressure ventilation use following conventional surfactant administration (LPPSA) are not inferior to LISA in the treatment of preterm infants with RDS.

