### Sample size calculation

The proposed sample size is calculated according to the incidence of BPD. According to previous reports and the average data from every unit involved in the trials [6, 7], approximately 60% of infants born at 25^+ 1^ to 27^+ 6^ gestational weeks and approximately 15% among those born at 28^+ 1^–31^+ 6^ gestational weeks have developed BPD during the past 5 years. The presumed incidence of BPD will be approximately 25% in the pooled population of our trial. Considering an alpha error rate of 0.05 and a power of 0.8 to detect an expected 20% reduction in the incidence of BPD, 258 infants will be enrolled in each group. To consider factors such as data incompleteness, failure to follow up, or early dropout, we plan to recruit 300 preterm neonates for each group.

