### Statistical methods

All data will be analyzed using SPSS version 20.0. To compare primary and secondary outcomes between the two groups, Student’s t-test (continuous variables) and the chi-squared test (categorical variables) will be used. The two-level hierarchical linear regression model or the logistic regression model, whichever is appropriate, will be applied for the comparison of the outcomes between the two groups, accounting for the infants’ characteristics, such as gestational age, birthweight, sex, appropriateness for gestational age, delivery mode, and pregnancy complications, and center variables, such as number of beds in the NICU and the number of infants with gestational age < 32 weeks. *P* < 0.05 will be regarded as statistically significant.

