## Discussion

In recent years, the LISA method has been accepted by increasing number of doctors. However, the potential benefit of LISA is still not clear. Moreover, an increased incidence of spontaneous intestinal perforation in extremely premature infants has been reported [15]. A meta-analysis showed that LISA showed effects on reducing the rate of MV during the first 72 h and the combination of BPD mortality and morbidity based on previous trials, which compared the effects of LISA with conventional surfactant technique (including intubation and ventilation by bagging or ventilator). We found that previous studies focused more on the procedure of performing LISA but less on the clarity of the potential mechanism [16, 17]. In fact, pulmonary compliance will change during the period of surfactant administration, and the peak pressure of ventilation barely changed spontaneously, even with use of a more advanced ventilator. A preliminary idea is that the whole procedure of surfactant administration without ventilation may contribute most to the advantages of LISA [18]. Thus, if correct, we would have further comprehension of LISA, and further knowledge would encourage more efforts on applying optimal peak pressure to surfactant delivery instead of trying to require all doctors to learn the method of LISA in China.

The delivery of surfactant as soon as possible has been known to help the distribution of the surfactant [19] In a previous study, the LISA procedure may took 0.5–5 min (average 2-3 min), which is longer than that of conventional method. Desaturation and apnea are the main complications of LISA [20, 21]. This situation is seldom seen in conventional surfactant administration. The contradiction of “time and effects” between LISA and conventional method may suggest some potential benefits of LISA. In this trial, the time required to perform the procedure would also be evaluated, because of the variable data of previous studies.We hope it will give us more information of the reason and a relatively standard operation of LISA can be set.

To our knowledge, this trial will be the first multicenter randomized controlled trial to evaluate the potential benefits of LISA and will give a more objective evaluation of LISA.

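### The stated hypothesis is non-inferiority of LPPSA to LISA, but the sample size and the tests are for a difference, with no margin, so the analysis as written cannot confirm it unless LPPSA proves significantly better

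*Protocol article*

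**What the plan says.** - **Hypothesis (Background, last paragraph).** The only between-arm hypothesis about outcomes is that "the effects of designated low positive pressure ventilation use following conventional surfactant administration (LPPSA) are not inferior to LISA". The Study aim is neutral: it speaks of comparing mortality, BPD and early ventilation between the two methods.
- **Sample size (Sample size calculation).** The calculation is based on BPD: "The presumed incidence of BPD will be approximately 25% in the pooled population of our trial". It continues "Considering an alpha error rate of 0.05 and a power of 0.8" "to detect an expected 20% reduction in the incidence of BPD", giving 258 per group, raised to 300 for incomplete data and losses. It does not say whether the 20% is relative or absolute, whether alpha is one- or two-sided, or which arm should have the lower rate.
- **Analysis (Statistical methods).** Outcomes are compared by t-test, chi-squared test and regression. The only criterion is that P < "0.05 will be regarded as statistically significant".
- **Not stated anywhere.** No margin is given, and no confidence limit is to be compared with one.

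**The concern.** A non-inferiority hypothesis and a test of difference answer different questions. The test asks whether the data rule out equality. The hypothesis asks whether the data rule out LPPSA being worse by more than a tolerable amount, and that amount is never given. Of the three possible results, a significant advantage for LPPSA would support the hypothesis and a significant advantage for LISA would count against it. A non-significant result, which is the likely one if the hypothesis is true, settles nothing.

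The sizing has the same conflict. If LPPSA is expected to be about as good as LISA, no reduction between these two arms is expected, yet the trial is powered to find one.

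What is at stake is the main conclusion. With P < 0.05 as the only rule, a non-significant result is the main way in which the hypothesis could appear to be supported, although it is compatible with a clinically relevant excess of BPD under LPPSA.

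**Working it through.** **Inputs.** From Sample size calculation: BPD 25%, alpha 0.05, power 0.80, a 20% reduction, 258 per group (300 with the allowance for losses; 258/300 = 0.86, so 14% loss). The true LPPSA rates and the margins below are assumptions for illustration. The 25% is given for the pooled population; I apply it to LISA in step 2 and to both arms in step 3.

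**1. The plan's own figure.** For two proportions, n per group = [z(α)·√(2p̄(1−p̄)) + 0.842·√(p1(1−p1) + p2(1−p2))]² / (p1−p2)², with p̄ the mean of the two rates.
- 25% to 20% (20% relative): 1094 two-sided (862 one-sided).
- 25% to 5% (20 points absolute): 49 two-sided (39 one-sided).
- 25% to 15%: 250 two-sided (270 with continuity correction).

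So 258 is not reproduced under either reading of the 20%; 25% to 15% comes nearest but is not what the text says. Two-sided power for 25% to 20% is 27% at 258 and 31% at 300. For 25% to 15% it is 81% at 258.

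**2. How often a worse LPPSA arm gives a non-significant result.** Let d be the true difference, s0 = √(2p̄(1−p̄)/n) and s1 = √([p1(1−p1) + p2(1−p2)]/n). Then P(non-significant) ≈ 1 − Φ((d − 1.960·s0)/s1); the opposite tail is negligible. At n = 258, with LISA at 25%:
- LPPSA 30%: (0.05 − 1.960×0.0393)/0.0393 = −0.69, so about 75%.
- LPPSA 32%: (0.07 − 1.960×0.0397)/0.0396 = −0.20, so about 58%.
- LPPSA 35%: (0.10 − 1.960×0.0403)/0.0401 = 0.52, so about 30%.

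At n = 300 the figures are about 72%, 52% and 24%.

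**3. What this size supports as a non-inferiority trial.** Take 25% in both arms and one-sided 0.025. The standard error is √(2×0.25×0.75/n): 0.0381 at 258 and 0.0354 at 300.
- Margin for 80% power = (1.960 + 0.842) × SE: 10.7 points at 258 and 9.9 points at 300.
- Power at 258 = Φ(margin/SE − 1.960): 10 points gives Φ(0.66) = 75%; 5 points gives Φ(−0.65) = 26%.
- Size per group for 80% power: 295 for 10 points, 1178 for 5 points.

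A 10-point margin on a base of 25% would accept a rate of up to 35%, which is a relative excess of 40%.

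**The case against.** The strongest defence is that the non-inferiority wording is one sentence in the Background, that the formal Study aim only compares, and that an unseen analysis plan or full protocol may hold the margin, the confidence-interval rule and the analysis sets. The last part is fair: the absence of those details alone would not be a finding. What stands is the conflict between things the article does state. A later plan would have to override the stated significance rule, and the sample size would still have been derived for a reduction to be detected.

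Some stronger readings are tempting, and the document does not support them:
- **That the authors will treat P ≥ 0.05 as proof of non-inferiority.** No passage says so. It is a risk created by having no other rule.
- **That the Discussion commits to acting on non-inferiority.** It suggests that what is learned may "encourage more efforts on applying optimal peak pressure to surfactant delivery instead of trying to require all doctors to learn the method of LISA", but the condition attached refers to a preliminary idea about why LISA works. That shows motive; it is not a plan or a decision rule.
- **That a worse LPPSA arm would usually escape detection.** At 258 per group this holds for true differences up to about 7 points. At 10 points the chance is 30%.
- **That losses and treatment failures will favour the hypothesis.** Bias from losses can go either way. The article describes no switch to the other trial arm, and under its own theory failures in the LPPSA arm would make LPPSA look worse.
- **That 258 hides a margin of 10.7 points.** The numbers coincide, but no margin is stated and the text describes detecting a reduction.

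**Conclusion.** The point holds in this form: the Background states non-inferiority, while the Sample size calculation and Statistical methods set up a test of difference with no margin. The stated analysis can confirm the stated hypothesis only if LPPSA is significantly better than LISA. The mismatch needs no assumption; it follows from the three sections read together.

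The size does rest on assumptions: 25% BPD under LISA, illustrative true LPPSA rates, a normal approximation and independent infants. On these, a true 5-point excess under LPPSA goes undetected about three times in four. The planned evaluable number has 80% power for non-inferiority only at a margin above 10 points. The main conclusion depends on which objective is meant, so this should be settled before any between-arm results are available.

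**What to change.** State one objective for one named primary outcome. BPD at 36 weeks PMA is the natural choice, since the trial is sized on it. Do this before any interim or between-arm data are seen; waiting for formal unblinding is too late, because care providers are not blinded and the monitoring committee is to carry out interim analysis. Then take one route.

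- **(a) Non-inferiority.** Pre-specify a margin on the LPPSA minus LISA risk difference and justify it clinically, without working back from the sample size. Claim non-inferiority only if the upper limit of the two-sided 95% confidence interval lies below the margin, and report both intention-to-treat and per-protocol results. Replace the present power statement with the power for that margin at the planned 258 evaluable per group, and show the figure for 300 beside it.
- **(b) Superiority.** If no margin can be defended, delete the non-inferiority hypothesis, call the trial a superiority comparison, report the risk difference with its 95% confidence interval, and state that P ≥ 0.05 will not be read as non-inferiority.

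In either case correct the sample size paragraph: state the two BPD rates, the direction and the sidedness. If a 20% relative reduction is meant, the stated power must fall to about 27% at 258 (31% at 300). If 25% to 15% is meant, it is about 81% at 258, and the text should say so.

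The cost is protocol and analysis-plan wording, one confidence-interval analysis and, under (a), a second analysis set, with no extra infants. The price is a less favourable stated power or a weaker claim.

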## Methods/design

### Study aim

This trial aims to compare the mortality and incidence of BPD at 36 weeks of PMA and the MV requirement during the first 72 h of life between LISA and LPPSA methods.

### Setting

The **L**ISA **O**r **L**ow **P**eak **P**ressure trial, a multicenter randomized prospective trial, will be conducted in 14 tertiary neonatal intensive care units (NICUs) in China from January 2019 to December 2020. The trial has been approved by the ethics committee of the Women’s Hospital School of Medicine, Zhejiang University. This protocol has been registered in the Chinese Clinical Trial Registry (ChiCTR1900020970). The diagram of the study protocol is presented in Fig. 1.

**Fig. 1 Fig1:**
[figure not shown]
Flow diagram of the trial protocol. *LPPSA* surfactant administration followed by low peak pressure ventilation, *PMA* postmenstrual age, *LISA* less invasive surfactant administration

### Grouping

Infants will be divided into two groups, namely, the LISA group or LPPSA group, according to the method of surfactant administration. Infants in the LISA group will receive surfactants by using a thin catheter (LISA catheter® designed by Shuanghe Pharmaceutical, Beijing). Infants will be on nasal continuous positive airway pressure (NCPAP) support during the course of surfactant administration. Infants in the LPPSA group will be given surfactant by traditional intubation and MV support with a T-piece or ventilator immediately following surfactant administration as done in INSURE but with a peak inspiratory pressure at < 15 cmH_2_O (12–15 cmH_2_O), positive end-expiratory pressure (PEEP) at 6–8 cmH_2_O, and respiratory rate at 40–60 breaths per minute.

### Inclusion criteria

Infants will be included if they meet all of the following criteria:
Born between 25^0/7^ and 31^6/7^ weeks of gestation with birth weight between 600 g and 1500 g.Exhibit vigorous spontaneous breathing and can be stabilized by noninvasive respiratory supportWith PEEP at 6–8 cmH_2_O and in need of fraction of inspired oxygen (FiO_2_) ≧0.3Less than 6 h of ageInformed parental consent has been obtained

### Exclusion criteria

Infants will be excluded if they meet any of the following:
Requiring MV or intubation in the delivery roomPresence of major congenital malformation or chromosomal abnormality or inherited disorders of metabolismHave neuromuscular diseases affecting respiratory functionPresence of congenital pneumonia or pulmonary hypoplasia

### Randomization

A randomization sequence with 600 numbers (odd to even numbers in a 1:1 ratio) will be generated by a computerized random number generator and placed in sealed opaque envelopes. Infants with odd and even numbers will be assigned to the LISA and LPPSA groups, respectively. Twins or multiple birth infants will be randomized separately. Every eligible infant will be allocated to each group according to a randomized sequence within 30 min by an independent person (a nurse in Women’s Hospital School of Medicine, Zhejiang University).

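### Siblings are randomised separately, but the stated analyses do not model the remaining correlation between them: the tests stay valid, at a small and possibly negligible cost in precision

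*Protocol article*

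**What the plan says.** All statements are in the protocol article.

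- **Randomization.** "A randomization sequence with 600 numbers (odd to even numbers in a 1:1 ratio) will be generated by a computerized random number generator", and "Twins or multiple birth infants will be randomized separately". No blocking or linking of siblings is described, so a twin pair may fall in one arm or be divided between the two.
- **Statistical methods, unadjusted.** "Student’s t-test (continuous variables) and the chi-squared test (categorical variables) will be used".
- **Statistical methods, adjusted.** "The two-level hierarchical linear regression model or the logistic regression model, whichever is appropriate, will be applied for the comparison of the outcomes". The infant-level list reads "accounting for the infants’ characteristics, such as gestational age, birthweight, sex, appropriateness for gestational age, delivery mode, and pregnancy complications"; the centre-level list reads "center variables, such as number of beds in the NICU and the number of infants with gestational age < 32 weeks".

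The two levels are not named; infant and centre are inferred from the covariate lists. It is also unclear whether the two-level structure extends to the logistic model. No family level, GEE or robust variance is mentioned. Multiple birth is absent from the covariates and from the items under Other data, and Sample size calculation has no sibling term.

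**The concern.** Siblings share gestational age, antenatal exposures and genes, so BPD, death and early ventilation are likely to be correlated within a family. The t-test and chi-squared test treat all infants as unrelated, and a model with only infant and centre levels has no term for what siblings share beyond the listed covariates.

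About half of twin pairs will be divided between the arms by chance. In those pairs the shared part of the outcome cancels from the treatment contrast, but an analysis that ignores the pairing leaves it in as noise. What is at stake is the width of the confidence interval, not the validity of the test. Width matters here because the Background frames the hypothesis as non-inferiority of LPPSA to LISA.

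**Working it through.** **The plan's own figure.** The article gives no figure for siblings. Its 258 per group treats infants as independent. From the stated rate ("The presumed incidence of BPD will be approximately 25% in the pooled population of our trial"), two-sided alpha 0.05 and power 0.8, a relative 20% reduction (25% to 20%) needs 1094 per group and an absolute one (25% to 5%) needs 49, so 258 does not reproduce. The nearest simple contrast, 25% v 15%, needs 250, or 270 with continuity correction. That is a separate matter. Below, 25% v 15% at 258 per group only illustrates power (0.81 for independent infants).

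**Inputs**
- From Randomization: 1:1 allocation, siblings allocated separately, 600 infants.
- Assumed, because the article gives neither: *f*, the share of infants from twin pairs (0.10 to 0.40), and *r*, the correlation of outcomes within a pair (0.2, 0.3, 0.5). For the adjusted model, *r* is the residual correlation after covariates. Higher-order multiples are ignored.

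**Information in a pair.** Code treatment as ±1/2 and scale the outcome to unit variance. An analysis that models the pair gains information

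(t₁² + t₂² − 2r·t₁t₂) / (1 − r²).

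- Divided pair: (1/2)(1 + r)/(1 − r²) = (1/2)/(1 − r).
- Same-arm pair: (1/2)(1 − r)/(1 − r²) = (1/2)/(1 + r).
- Average over equal chances: (1/2)/(1 − r²).

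Two unrelated infants give 1/2. The gain for the whole trial is therefore

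**gain = f × [1/(1 − r²) − 1].**

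The bracket is 1/0.96 − 1 = 0.0417 at r = 0.2, 1/0.91 − 1 = 0.0989 at r = 0.3, and 1/0.75 − 1 = 0.3333 at r = 0.5.

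| r | f = 0.10 | f = 0.20 | f = 0.30 | f = 0.40 | Equivalent infants of 600 (f = 0.10 to 0.40) |
|---|---|---|---|---|---|
| 0.2 | 0.4% | 0.8% | 1.3% | 1.7% | 2.5 to 10 |
| 0.3 | 1.0% | 2.0% | 3.0% | 4.0% | 6 to 24 |
| 0.5 | 3.3% | 6.7% | 10.0% | 13.3% | 20 to 80 |

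**Type I error of the test that ignores pairing.** Same-arm pairs raise the true variance above the naive one and divided pairs lower it; under separate allocation the two balance on average. Simulation agrees:
- 20,000 trials of 600 infants, event rate 25%, r = 0.5: 5.0% (f = 0.3) and 4.8% (f = 0.4).
- A second simulation of 8,000 trials per scenario, f = 0.3 to 0.4, r = 0.30 to 0.56: 4.9% to 5.3%.

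**Check of the precision formula (8,000 trials, null).** Variance of the sibling-aware estimate relative to the naive one:
- f = 0.3, r = 0.302: simulated 0.974; formula 1/(0.7 + 0.3/(1 − 0.302²)) = 0.971.
- f = 0.3, r = 0.561: simulated 0.880; formula 0.879.
- f = 0.4, r = 0.561: simulated 0.837; formula 0.845.

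**Power at 258 per group, 25% v 15% (8,000 trials each)**

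| f | r | Ignoring pairs | Modelling pairs |
|---|---|---|---|
| 0.2 | 0.29 | 0.816 | 0.821 |
| 0.3 | 0.29 | 0.822 | 0.829 |
| 0.3 | 0.53 | 0.817 | 0.854 |
| 0.4 | 0.53 | 0.819 | 0.868 |

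The last two rows use a correlation slightly above the top of the assumed range.

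**The case against.** The strongest objection is that nothing invalid is planned. Allocating siblings separately and testing at infant level keeps the 5% error rate and introduces no bias, so the point is about efficiency only. **This stands**, and it keeps the severity low.

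A second objection is that sibling terms belong in a fuller protocol or SAP, that the covariate lists are open-ended, and that the case report form is not shown. **This stands in part.** A sibship identifier may already be recorded, and the article should not be read as showing that it is not. But the article does state both a sibling-allocation rule and a two-level structure, so the remark concerns a stated analysis and not only missing detail.

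A third objection is that the adjusted model already includes gestational age, delivery mode and pregnancy complications, which siblings wholly or largely share, and centre variables. **This stands.** Part of the sibling correlation is absorbed, so only the residual ICC counts there. The share may also be low, because both siblings must individually meet the eligibility criteria for a pair to count.

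Two stronger readings are tempting:
- *The planned tests inflate false positives.* In simulation the naive error rate rises to 6.3% to 7.2% only if pairs always share an arm, and falls to 2.5% to 3.9% if they are always divided. The protocol plans neither.
- *The design creates matched pairs whose information is thrown away.* Only about half of pairs are divided, by chance, and the shared covariates recover part of the information.

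**Conclusion.** The point holds as one of modest efficiency. The stated analyses do not model residual sibling correlation. They remain valid, with type I error of about 5%, and lose some precision.

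The size rests entirely on two assumed quantities. At a low share or low residual ICC the gain is negligible: 0.4% to 2% at ICC 0.2, and 1% to 4% at ICC 0.3. It reaches 13% only with 40% of infants from twin pairs and an ICC of 0.5. The conclusion also rests on reading the two levels as infant and centre, which the article implies but does not state. Low severity: a cheap improvement, not a correction of an error.

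**What to change.** 1. Make sure that a mother or sibship identifier is available for every infant. If it is not already recorded, this is one data field. Trial status says recruitment is ongoing, so it is easiest to capture now.
2. In Statistical methods, pre-specify for the primary outcomes one marginal model: GEE clustered on the mother, with exchangeable working correlation, robust standard errors, and centre and the listed covariates in the model. Do not offer a mother random-intercept logistic model as an alternative. It estimates a mother-specific odds ratio, so switching between the two would change the estimand.
3. Name a fallback for non-convergence: independence GEE with mother-clustered robust errors. It keeps the marginal estimand and valid errors, but the plan should say that it gives no precision gain. In 20,000 simulated trials at 258 per group, 25% v 15%, power for the naive v the robust analysis was 0.814 v 0.812 (f = 0.3, r = 0.3), 0.811 v 0.808 (f = 0.3, r = 0.5) and 0.818 v 0.812 (f = 0.4, r = 0.5).

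**Cost.** At most one data field, a sentence or two of text and slightly more analysis work; no extra infants. Many clusters will be single infants, and the gain may prove negligible.
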